### 8.9.2 Participant questionnaires

The following questionnaires will be sent to participants in the intervals above. These will be posted or emailed by the Clinical Trials Unit and can be completed by post or online. If participants do not respond within 2 weeks of sending the questionnaire, a reminder will be sent. Following this, if still no response, the central trial team may telephone the participant to collect the required data.

- Impact of Hand Nerve Disorder (I-HaND) v2  
I-HaND v2 is a validated patient-reported questionnaire specific to hand nerve disorder that measures symptoms, activity limitations and participation restrictions (23).
- Hand Health Profile of the Patient Evaluation Measure  
This questionnaire includes three sections: treatment, hand health profile and overall assessment. For the NEON study only section two, the hand health profile is being used. Similarly to I-HaND v2, this questionnaire asks about symptoms and activity limitations (24).
- EQ-5D-5L  
This questionnaire will be completed in order to calculate the EQ-5D-5L index (UK population weights) and EQ-VAS, and from this estimate quality adjusted life years for trial-based economic evaluation (25, 26).
- Complications  
Participants will report early complications 6 weeks post randomisation. These will include wound infection, delayed healing and re-opening, scar sensitivity and persistent ongoing pain.

- **Health Resource Use**

Postoperative costs and lost productivity costs attributable to the injured digital nerve will be collected during the 12-month follow-up period. This includes information on outpatient visits, community care provision, and days off work due to injury.

## **8.10. Long term follow up**

To obtain long term data about participants beyond the 12 month primary endpoint, data will be collected via two established methods:

### **Hospital Episode Statistics (HES) data**

Routinely collected HES data will be used to determine re-operation rates on study participants 1-2 years following initial surgery. A bespoke HES extract linked to the Office of National Statistics data is required.

### **Long term follow up delivered by RSTN**

On completion of 12 month follow up, long term data collection will take place using the RSTN. This will engage surgical trainees based at each of the study hospitals. They will review local routinely collected data of the study participants to identify any further procedures or complications (e.g. complex regional pain syndrome and neuroma formation). This data will be collected as part of a routine audit by RSTN.

## **8.11. Early Discontinuation/Withdrawal of Participants**

During the course of the study, a participant may choose to withdraw from the randomised intervention or other study procedures at any time. This may happen for several reasons, including but not limited to:

- Investigator decision
  - Ineligibility (either arising during the study or retrospectively having been overlooked at screening)
  - Other clinical reasoning
  - Significant protocol deviation
  - Significant non-compliance with treatment regimen or study requirements
- Participant decision
  - The occurrence of what the participant perceives as an intolerable adverse event
  - Inability to comply with study procedures

The type of withdrawal and reason for withdrawal will be recorded in the relevant Case Report Form (CRF). If the participant is withdrawn due to an adverse event, the Investigator will arrange follow-up until the adverse event has resolved or stabilised.

Participants may decide any of the following types of withdrawal:

- Withdrawal from clinical assessment visits but willing to complete questionnaires at home.
- Withdrawal from clinical assessment visits and completing questionnaires, but willing for the study team to access medical records and any relevant hospital data that is recorded as part of routine care. These participants may also be willing to be followed up via HES and the RSTN.
- Withdrawal from all follow-up, but willing for data collected up to the point of withdrawal to be included in the final study analysis.

- Complete withdrawal, with data collected not being used in the final study analysis. (There are limits to this, for example when data has already been integrated into interim results.)

All participants who withdraw from the study will continue to receive routine clinical care.

Participants will not be replaced, as withdrawal and loss to follow-up has been accounted for in the estimated sample size. Analysis will be performed as per intention-to-treat, irrespective of compliance with treatment allocation.

## **8.12. Definition of End of Study**

The end of the initial follow-up is defined as 30 days after the final participant visit, and after all the data has been entered and queries resolved. The end of the trial is defined as 1 year after this point, and when all longer term follow-up data has been entered, queries resolved, analysis completed and dissemination undertaken.

## **9. SAFETY REPORTING**

The study involves no additional risks to participants beyond those of routine standard care. Participants will be informed of the standard risks associated with the anaesthetic and surgery.

Complications that the clinicians deem associated with the patient population and the study treatments will be reported by participants and assessed at study-specific clinic visits. Examples of expected complications include, but are not limited to:

- Wound infection, over granulation, delayed healing and re-opening
- Scar sensitivity, redness and abnormality
- Neuroma
- Lack of sensitivity
- Hypersensitivity
- Cold intolerance
- Complex regional pain syndrome
- Flexor tendon re-rupture, stiffness and swelling

Complications will be periodically reviewed by the Data Monitoring Committee (DMC) and any unusual increased patterns of serious adverse events (ie complications defined as serious) compared to what is expected for such patients and interventions will be notified to the REC.

### **9.1. Reporting Procedures for Unexpected Serious Events**

An event occurring to a participant should be reported to the REC that gave a favourable opinion of the study where, in the opinion of the Chief Investigator (CI) the event was:

1. Serious according to the definitions in section 9.2
2. Related – resulted from administration of any of the research procedures
3. Unexpected in relation to those procedures

Sites need to submit reports of such events within 24 hours of the Principal Investigator becoming aware of the event. The central study team will then submit to the REC within 15 days of the CI becoming aware of the event.

No other adverse events will be reported.

## 9.2. Definition of Serious Adverse Events

A serious adverse event is any untoward medical occurrence that:

- results in death
- is life-threatening
- requires inpatient hospitalisation or prolongation of existing hospitalisation
- results in persistent or significant disability/incapacity
- consists of a congenital anomaly or birth defect.

Other 'important medical events' may also be considered a serious adverse event when, based upon appropriate medical judgement, the event may jeopardise the participant and may require medical or surgical intervention to prevent one of the outcomes listed above.

The term "life-threatening" in the definition of "serious" refers to an event in which the participant was at risk of death at the time of the event; it does not refer to an event which hypothetically might have caused death if it were more severe.

## 10. STATISTICS AND ANALYSIS

### 10.1. Statistical Analysis Plan (SAP)

The statistical aspects of the study are summarised here with details fully described in a statistical analysis plan that will be finalised before the final analysis takes place and agreed by the Trial Steering Committee (TSC).

### 10.2. Description of the Statistical Methods

The primary outcome measure (I-HaND v2) will be compared using a linear regression model with adjustment for the minimisation variables (critical or non-critical zone, associated tendon injury and study site). Study site will be accounted for using cluster robust variance. A secondary unadjusted analysis will also be carried out by an independent t-test. Secondary outcomes will be analysed using generalised linear models with adjustment for minimisation factors and baseline variables as appropriate. Where appropriate, repeated data will be used. Exploratory subgroup analyses will explore the possible treatment effect modification of clinically important factors (nerve injury type and critical location involvement or not), through the use of treatment by factor interaction, and will be interpreted cautiously.

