## 7.3. Inclusion Criteria

Patients aged 18 years and above with a suspected complete digital nerve laceration in any single digit, including thumb and little finger, appropriate for surgical repair.

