## **8.7. Baseline Assessment**

It is not possible to collect pre-injury baseline data. Injury details will be collected as part of the operative assessment, rather than as a separate baseline data.

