### 10.3. Sample Size Determination

Based upon I-HaND data for patients with hand nerve conditions and our recent sample of digital nerve patients, the standard deviation (SD) could be as high as 21 points (23). To detect a target mean difference of 7 points (previous work in a similar measure suggests 7 would be an important difference; 0.3 standardised effect size) in the I-HaND with an SD of 21, 2-sided 5% significance level and 90% statistical power, 191 participants will be required per group (382 overall) (14, 27, 28). Based on the team's experience of other digital nerve studies and hand trials 20% missing data has been allowed for giving an overall target of 478.

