## 20. APPENDIX A: SCHEDULE OF STUDY PROCEDURES

NB only inclusive of the first 12 months of study participation

| Procedures                                                           | Visits    |           |         |          |          |           |
|----------------------------------------------------------------------|-----------|-----------|---------|----------|----------|-----------|
|                                                                      | Screening | Operation | 6 weeks | 3 months | 6 months | 12 months |
| Eligibility assessment                                               | X         | X         |         |          |          |           |
| Informed consent                                                     |           | X         |         |          |          |           |
| Demographics                                                         |           | X         |         |          |          |           |
| Injury details                                                       |           | X         |         |          |          |           |
| Randomisation                                                        |           | X         |         |          |          |           |
| Surgery details                                                      |           | X         |         |          |          |           |
|                                                                      |           |           |         |          |          |           |
| Impact of Hand Nerve Disorders (I-HaND)                              |           |           | X       | X        |          | X         |
| Hand Health Profile of the Patient Evaluation Measure                |           |           |         |          |          | X         |
| EQ-5D-5L questionnaire                                               |           |           | X       | X        | X        | X         |
| Health resource use questionnaires                                   |           |           |         | X        | X        | X         |
| Perception of treatment                                              |           |           |         |          |          | X         |
|                                                                      |           |           |         |          |          |           |

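### Age, known at entry, could be prespecified as a further covariate in the primary I-HaND model: a potential gain in precision at almost no cost

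*Protocol*

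**What the plan says.** Protocol section 10.2 describes the primary analysis as a "linear regression model with adjustment for the minimisation variables (critical or non-critical zone, associated tendon injury and study site"). It then says: "Study site will be accounted for using cluster robust variance". On that wording, only two binary factors, critical zone and tendon injury, clearly enter the mean part of the model. An unadjusted t-test is planned as a secondary analysis.

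The same section is more generous to the other outcomes: "Secondary outcomes will be analysed using generalised linear models with adjustment for minimisation factors and baseline variables as appropriate".

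Three other places bear on which covariates are available:

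- Section 8.7 states: "It is not possible to collect pre-injury baseline data". Appendix A first schedules I-HaND at 6 weeks, so no pre-treatment score exists.
- Section 7.3 admits "Patients aged 18 years and above with a suspected complete digital nerve laceration in any single digit", so age has to be known before randomisation.
- Appendix A has a row headed "Demographics" at the operation visit. It does not list the items.

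Age is not among the minimisation factors in section 8.4.

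**The concern.** When a patient-reported outcome is also measured at baseline, that score is usually the covariate that buys most precision. Here it does not exist, so the primary model relies on a short list of injury factors. The secondary models may draw on further baseline variables, and section 10.2 gives no reason for the difference.

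Age is fixed before randomisation and has to be checked for eligibility. Because allocation is not balanced on it, the arms can differ in age by chance. In a linear model, adding a prespecified pre-randomisation covariate leaves the quantity estimated, the difference in mean I-HaND, unchanged. If the covariate is related to outcome, the residual variance falls and a chance imbalance is corrected. What is at stake is a narrower interval for the trial's main result. Neither its validity nor its planned power is in question.

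**Working it through.** **Inputs.** From section 10.3: target difference 7 points, two-sided 5% significance, 90% power, 191 per group (382 overall), 20% missing data, total 478. On the SD the section says "the standard deviation (SD) could be as high as 21 points (23"). From section 8.4: 1:1 allocation. Assumed, because the protocol gives no value: r, the correlation of age with I-HaND given the factors already in the model, taken as 0, 0.1, 0.2 or 0.3.

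**Step 1: reproduce the plan's own figure.** The normal approximation gives 190 per group. The noncentral t calculation gives 191 per group, so 382 overall. Allowing for missing data, 382 / 0.8 = 477.5, rounded up to 478. The stated sample size is confirmed, and it takes no credit for any covariate.

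**Step 2: effect of adding age.** The residual SD becomes

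SD(r) = 21 × √(1 − r²).

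With 191 analysed per group, the standard error of the difference is SD(r) × √(2/191), and the 95% half-width is 1.96 times that. At r = 0 this is 1.96 × 21 × √(2/191) = 4.21 points. Power is from the noncentral t distribution with 2 × 191 − 2 = 380 degrees of freedom. The last column is the number of extra analysed participants that would give the same gain, 382 × (1/(1 − r²) − 1).

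| Assumed r | Fall in residual variance (r²) | Residual SD | Power | 95% CI half-width | Equivalent extra participants |
|---|---|---|---|---|---|
| 0 | 0% | 21.00 | 90.1% | 4.21 | 0 |
| 0.1 | 1% | 20.89 | 90.4% | 4.19 | about 4 |
| 0.2 | 4% | 20.58 | 91.3% | 4.13 | about 16 |
| 0.3 | 9% | 20.03 | 92.6% | 4.02 | about 38 |

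At r = 0.3 the interval is narrower by (4.21 − 4.02) / 4.21 = 4.5%, and power is higher by 92.6 − 90.1 = 2.5 percentage points.

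**Step 3: limits of the calculation.** It is a plain two-sample comparison. The planned model also contains two injury factors, which is why r must be read as a partial correlation, and it uses cluster robust variance by site, which the calculation ignores. The table therefore shows the order of size of the gain and does not predict the planned model's power.

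**The case against.** The strongest reply is that nothing here is wrong. Adjusting for the minimisation factors is the natural analysis after minimisation, and the stated power is met without age. Treating primary and secondary outcomes differently is not a contradiction, since baseline variables are allowed for the latter only as appropriate across several outcome types. All of that stands.

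It also stands that the protocol gives no evidence on how strongly age predicts I-HaND in these adults. The only hint is the title of a cited study in children, which says nothing about size. If r is zero, nothing is gained.

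A reader might infer several stronger things that the document does not support:

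- **That the plan gives away precision for certain.** That needs a non-zero r, which is assumed here and not shown.
- **That age is the only prognostic covariate to hand.** Injury and surgery details are also recorded at operation (section 8.8 and Appendix A), and two injury factors are already in the model.
- **That age is certain to be recorded and complete.** Eligibility requires it to be known, but Appendix A does not name the demographic items.
- **That the observed-data analysis is at risk without age.** This would matter if loss to follow-up depended on age, but the protocol gives no sign that it does. Section 10.7 already plans sensitivity analyses for missing primary outcome data, including data missing not at random.

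A last objection is that section 10.1 leaves details to the statistical analysis plan, which could add covariates, and that section 10.2 does not say its list is exhaustive. This does not remove the point. The protocol itself states the primary covariates, so an analysis plan that added age would be extending that list, and the protocol is a proper place to settle it.

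**Conclusion.** The point holds as a free improvement and not as an error. The primary model is valid and adequately powered as written. An available pre-randomisation covariate is left out of it, while the secondary models may use such variables.

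The gain is conditional. Over the assumed range of r from 0 to 0.3, power moves from 90.1% to at most 92.6%, and the 95% half-width from 4.21 to at best 4.02 points. This rests on three assumptions: the planning SD of 21, 191 analysed per group, and age being recorded for all participants. The case for acting is that the cost is close to nothing even if r proves to be zero.

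**What to change.** In section 10.2, name age (continuous) as a prespecified covariate in the primary regression, alongside critical zone, tendon injury and site. Keep the unadjusted t-test as the planned secondary analysis. Confirm that age is an item in the demographic data taken at operation.

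The cost is one added model term and one degree of freedom out of about 380. No new data are needed, and neither the sample size nor the estimand changes. If the sponsor prefers to leave age out, a sentence explaining why baseline variables are open to the secondary models but not to the primary one would settle the matter.

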## 7. STUDY DESIGN

NEON is a multicentre randomised controlled trial with 1:1 allocation. Participants and follow-up assessors will be blinded to the randomised allocation.

Participants will be recruited to the study in hospitals across the UK. The study overall is modelled on 25 centres, but additional sites may be included depending on recruitment rates in the 9 month recruitment pilot phase.

Participants are expected to be enrolled in the study for up to 24 months. During the first 12 months the participants will attend follow-up clinic visits and complete questionnaires as per the schedule in Appendix

A and flow diagram (Figure 1). Routine data will be collected during the second 12 months via HES data and the Reconstructive Surgical Trainees Network (RSTN).

[figure not shown]

**Figure 1:** Participant flow diagram for NEON study

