### **10.7. Procedure for Accounting for Missing, Unused, and Spurious Data.**

Principal analyses will be based upon observed data without imputation. The impact of missing data will also be explored in sensitivity analyses of the primary outcome and key secondary outcome (EQ-5D-5L) utilising using appropriate methods (e.g. the `rctmiss` Stata command for assessing the impact of missing not at random using a pattern mixed-model based approach) (29, 30).

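### Section 10.2 leaves unclear whether the 6-week and 3-month I-HaND scores enter the primary analysis, and it handles site only through a cluster-robust variance that is unstable with about 25 sites

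*Protocol*

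**What the plan says.** Section 10.2 sets the primary analysis: "The primary outcome measure (I-HaND v2) will be compared using a linear regression model with adjustment for the minimisation variables". It lists those variables as zone, tendon injury and study site. The next sentence reads: "Study site will be accounted for using cluster robust variance". A companion analysis follows: "A secondary unadjusted analysis will also be carried out by an independent t-test". After the sentence on secondary outcomes comes: "Where appropriate, repeated data will be used". Section 10.2 names no time point for the primary comparison.

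Other sections bear on how this is read:
- Sections 3 and 6 and Appendix A give I-HaND at 6 weeks, 3 months and 12 months. Section 8.10 calls 12 months the primary endpoint, but only in passing. Appendix A has no I-HaND before surgery.
- Section 10.7 states: "Principal analyses will be based upon observed data without imputation". It adds sensitivity analyses for missing data on the primary outcome, including a missing-not-at-random approach.
- Section 10.3 allows for 20% missing data (382 analysed, 478 randomised).
- Section 7 states: "The study overall is modelled on 25 centres", with more sites possible. Section 8.4 allocates individuals 1:1, minimised by site, zone and tendon injury.

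**The concern.** There are two linked points, both about what section 10.2 fixes.

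**Site.** The text promises adjustment for site and then deals with site only in the variance. A cluster-robust variance changes the standard error and leaves the fitted mean unadjusted for site. It is estimated from about 25 clusters, probably of unequal size, so the standard error is itself noisy. The interval and p-value for the main result then depend on a poorly estimated quantity.

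**Earlier scores.** A linear regression paired with a t-test uses one score per participant. Taken with a 12-month endpoint and observed data only, anyone without a 12-month score drops out of the principal analysis, even if they returned I-HaND at 6 weeks and 3 months. With no pre-surgery I-HaND, those are the only earlier values of the primary outcome. If people leave because of how they were recovering, and do so differently by arm, the principal estimate shifts although data that could correct much of it are in hand.

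**Working it through.** **1. The plan's own figure.** Inputs from section 10.3: difference 7, SD 21, two-sided 5%, power 90%.
- n per arm = 2(1.960 + 1.282)² × 21²/7² ≈ 189.1, so 190. The t-based version gives 190.1, so 191, or 382 in all. 382/0.8 = 477.5, so 478. The plan's numbers reproduce.
- With 239 × 0.8 = 191.2 observed per arm, SE = 21 × √(2/191.2) = 2.148. Power = Φ(7/2.148 − 1.96) = 90.3%.

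**2. Site.** Simulated trials: 382 analysed, 25 sites, SD 21, allocation balanced within site, no treatment-by-site variation, 3,000 runs per row (Monte Carlo error about 0.4 points). Robust variance has the usual G/(G−1) correction except where marked. The coefficient of variation (CV) of site size and the intraclass correlation (ICC) are assumptions, as the protocol gives neither.

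| Site-size CV | ICC | Run-to-run variation of SE: robust / site effects | Coverage, robust t(24) | Robust, normal | Uncorrected, normal | Site effects | Mean half-width: robust t(24) / site effects |
|---|---|---|---|---|---|---|---|
| 0 | 0.03 | 15.0% / 3.7% | 94.8% | 93.7% | 93.1% | 94.9% | 4.35 / 4.17 |
| 0.8 | 0.03 | 17.9% / 3.8% | 93.8% | 92.6% | 91.9% | 94.4% | 4.28 / 4.18 |
| 1.2 | 0.03 | 19.9% / 3.8% | 93.7% | 92.5% | 91.8% | 94.8% | 4.20 / 4.18 |
| 0.8 | 0 | 17.5% / 3.7% | 93.9% | 92.6% | 92.0% | 95.1% | 4.33 / 4.24 |
| 0.8 | 0.10 | 17.3% / 3.8% | 95.0% | 94.0% | 93.6% | 95.2% | 4.13 / 4.03 |

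With t(24) the shortfall from 95% is 0 to 1.3 points. With a normal reference it is 1.0 to 2.5. Repeat simulations gave type I error of 5.1-5.3% with equal sites, 5.7-5.8% at CV 0.8 and 6.7-6.9% at CV 1.2, so the extreme row is uncertain by roughly half a point. At CV 0.8 and ICC 0.03, coverage with the t reference was 94.6% at 40 sites and 94.2% at 15.

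The true spread of the estimate is the same with and without site effects: 2.163 and 2.166 at ICC 0.03, and 2.035 and 2.039 at ICC 0.10 (both CV 0.8).

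If the effect truly varies between sites (SD 4 points, assumed), coverage is 93.8% for the robust variance and 91.7% for site fixed effects.

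**3. Precision from the early scores.** Assume 20% missing at 12 months, exchangeable correlation ρ between visits, and a share q of those missing at 12 months having both earlier scores. Then R² = 2ρ²/(1+ρ), and the variance of the 12-month difference relative to the 12-month-only analysis is 1 − R²[1 − 0.8/(0.8 + 0.2q)].

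| ρ | q | Variance ratio | SE | Power |
|---|---|---|---|---|
| 0.4 | 0.5 | 0.975 | 2.12 | 91.0% |
| 0.6 | 0.5 | 0.950 | 2.09 | 91.7% |
| 0.6 | 1 | 0.910 | 2.05 | 92.7% |
| 0.8 | 1 | 0.858 | 1.99 | 94.1% |

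For ρ = 0.4, q = 0.5: R² = 0.32/1.4 = 0.229, and 1 − 0.229 × 0.111 = 0.975. The gain is about 2.5% to 14% of variance.

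**4. Bias.** The complete-case bias in an arm is about SD × ρ × (shift in the mean standardised 3-month score among those who stay). Assume about 20% missing, ρ from 0.5 to 0.7, and dropout odds doubling per SD of the 3-month score.
- One arm only: simulated bias is 1.4-2.0 points, or 20-29% of the 7-point target. A repeat gave 1.35-1.92. The lower figure implies a shift of 1.35/(21 × 0.5) = 0.129 SD, and 21 × 0.7 × 0.129 = 1.90, so the two ends agree.
- The same scenario with the 3-month score used: about 0 if all those missing at 12 months have it, and 0.5-0.7 if 60% do.
- The same dependence in both arms: complete-case bias is 0 under the null and 0.1-0.3 points with true effects of 3-7 points.

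**The case against.** The strongest reply is that both models are acceptable and the protocol leaves room for either. Much of it stands.

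- A reader might infer that the protocol commits itself to discarding the early scores. It does not. Section 10.2 names no time point, its repeated-data sentence might reach the primary outcome, and a likelihood model for all visits would also use observed data without imputation. The 12-month-only reading is the natural one, but it remains an inference.
- A reader might infer that robust intervals are too narrow. On average they are not: 4.13-4.35 points with t(24), against 4.03-4.24 with site effects. The shortfall comes mainly from noise in the standard error. The small-sample correction and reference distribution may properly be left to the statistical analysis plan.
- A reader might infer that between-site variance stays in the estimate. Minimisation by site makes allocation nearly balanced within site, and the simulated spread is the same either way.
- A reader might infer that the trial result will be biased by 1.4-2.0 points. That needs dropout that differs by arm. Participant blinding and identical follow-up (section 8.5), with reminders and telephone collection (section 8.9.2), make this less likely, and section 10.7 already plans sensitivity analyses.
- Robust variance does better if the effect varies by site, which is plausible for surgery.

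What the reply does not remove is the mismatch between listing site as an adjustment variable and handling it only in the variance, the silence on the time point, and the noisy standard error. The sensitivity analyses do not change the headline estimate, and section 10.7 does not say that they use the earlier scores.

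**Conclusion.** The point holds as an inexpensive improvement and a clarification. It does not make the trial invalid. With about 25 sites, the robust standard error varies by about 15-20% between trials, against about 4% with site effects. Under-coverage is about 0 to 1.5 points with t(24), and more with a normal reference. Leaving out the early scores costs roughly 2.5-14% of variance and some protection against dropout that depends on early recovery differently by arm.

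The sample size reproduces, and omitting the early scores does not take power below the stated 90%. These sizes rest on assumed site-size imbalance, ICC, between-visit correlation, availability of early scores and dropout mechanism, none of which the protocol gives. Site fixed effects stood in for site adjustment, and the full mixed model was not itself simulated. Priority: consider.

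**What to change.** In section 10.2, name the 12-month I-HaND contrast as the primary result. Estimate it from a linear mixed model for I-HaND at 6 weeks, 3 months and 12 months, with treatment-by-time, zone and tendon injury as fixed effects, site as a random intercept (or fixed effect) and an unstructured within-participant covariance. Keep the 12-month regression with cluster-robust variance as a sensitivity analysis, which also covers a treatment effect that varies by site. Keep the missing-not-at-random analyses in section 10.7, and say there that the principal analysis uses all observed I-HaND scores.

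The cost is wording in sections 10.2 and 10.7, with no new data or visits. The change should be made before outcome data are seen by arm, so that the choice cannot look data-driven. The downside is a slightly more complex model that assumes missing at random and, without a random treatment slope, would under-cover if the effect differs between sites.
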